Several studies have been conducted to explore the health-enhancing qualities of Tai Chi for stroke patients. The studies conducted by Taylor *et al*. demonstrated that community-based Tai Chi practice was a safe and feasible program for stroke patients[16, 17]. Another study indicated that a 12-posture short-form Tai Chi exercise was helpful in enhancing the standing balance of patients with a stroke history longer than 6 months after onset[18]. To the best of our knowledge, there has been no study to date in which Tai Chi was used in a rehabilitation program for stroke patients in the recovery phase (2 to 24 weeks). In this study protocol article, we will describe the rationale, design and analytic methods of a randomized controlled trial designed to investigate the rehabilitative effects of Tai Chi among hospitalized stroke patients in the recovery phase. We hypothesized that patients in the Tai Chi group would demonstrate better improvement compared with that in the control group.

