### Primary outcomes

The first primary outcome measurement is the recovery of motor impairment. We will apply the Fugl-Meyer Assessment (FMA) to measure it. Developed as the first quantitative evaluative instrument for measuring sensorimotor stroke recovery, the FMA is a well-designed, feasible and efficient clinical examination method that has been tested widely in the stroke population across different stroke recovery time points[21]. The FMA motor scale is recommended highly as a clinical and research tool for evaluating changes in motor impairment following stroke[22]. Its primary value is the 100-point motor domain, which has received the most extensive evaluation. It includes an assessment of the upper extremity and the lower extremity. In the present study, we will focus on the measurement of the lower extremity, which includes two subsections—the leg and coordination—with a total possible score of 34.

The improvements in activities of daily living that can be measured with the Barthel Index (BI) will be listed as another primary outcome measurement. The BI is a frequently used functional outcome measure of activities of daily living in stroke trials[23]. It is also widely used in clinical practice to assess baseline abilities, to quantify functional changes after rehabilitation and to inform discharge planning. The scale describes ten task items and is scored according to the amount of time or assistance required by the patient. These ten items are feeding, bathing, grooming, dressing, continence of bowels and bladder, transferring to and from a toilet, moving from wheelchair to bed and return, walking on a level surface for 45 meters and going up and down stairs. The total score ranges from 0 to 100, with lower scores representing greater nursing dependency[24].

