### Statistical analysis

Statistical analysis will be conducted by statisticians who are independent from the research team using SPSS 12.0 software for Windows (IBM SPSS, Chicago, IL, USA). The categorical variables will be presented with frequencies or percentages, and the continuous variables will be presented as means and standard deviations. Demographic and clinical assessments of two groups will be compared upon admission to address the baseline characteristics. For both groups, data of primary and secondary outcome measurements collected after 4 weeks and at the end of 3 months will be compared with baseline data, respectively, to evaluate the rehabilitative effects within groups. To evaluate the effects of Tai Chi on stroke rehabilitation, data of all outcome measurements after 4 weeks and at the end of 3 months will be compared between the two groups. Unpaired two-sample *t*-tests (continuous data) and χ^2^ analysis (categorical data) will be applied in data analyses between two groups. Nonparametric methods will be used when assumptions of normality are violated. Patients with missing data before 4 weeks will be eliminated. We will also conduct an intention-to-treat analysis if participants are lost to follow-up at 3 months. The statistical significance threshold will be set at 0.05 (two-sided), with 95% confidence intervals.

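### The between-group tests leave out the baseline score, although the hypothesis is about improvement and baseline is measured on every scale: a loss of precision, not a bias

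*Protocol article*

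**What the plan says.** The Background of the protocol article sets the question: "We hypothesized that patients in the Tai Chi group would demonstrate better improvement compared with that in the control group". The Primary outcomes section words two of the three primary measures the same way. For the Fugl-Meyer Assessment it says "The first primary outcome measurement is the recovery of motor impairment", and for the Barthel Index "The improvements in activities of daily living that can be measured with the Barthel Index (BI) will be listed as another primary outcome measurement". Balance (Berg Balance Scale) is worded there as an ability, but the Abstract puts all three scales under recovery.

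Study design and setting has every assessment done at baseline, 4 weeks and 3 months. Under Randomization and allocation concealment, the envelope is opened only after baseline testing.

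The Statistical analysis section uses the baseline scores in two places:

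- Within each group, the 4-week and 3-month data "will be compared with baseline data, respectively, to evaluate the rehabilitative effects within groups".
- At entry, "Demographic and clinical assessments of two groups will be compared upon admission to address the baseline characteristics".

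For the effect of Tai Chi itself, "data of all outcome measurements after 4 weeks and at the end of 3 months will be compared between the two groups". Unpaired t-tests (continuous data) and chi-square tests (categorical data) "will be applied in data analyses between two groups". The fallback is "Nonparametric methods will be used when assumptions of normality are violated". No change score, covariate or model is named.

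**The concern.** Part of the spread in a follow-up Fugl-Meyer, Barthel or Berg score is the level at which the patient started. The trial measures that level before allocation and then leaves it out of the one comparison that answers its question. Two things follow. The confidence interval is wider than the collected data require, in a trial that expects only 20 analysed per arm. Also, any chance difference in starting level between two small groups stays in the estimated effect. The article describes allocation from a computer-generated list and mentions no stratification by baseline score.

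This is not a detail left to an analysis plan. The article names both the data to be compared and the test, so it is a stated choice, and one that serves the stated question poorly.

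**Working it through.** **Inputs from the article.** 20 participants per group, 25% dropout, 25 recruited per group (Randomization and allocation concealment); two-sided 0.05 (Statistical analysis). No SD, effect size, power or baseline-to-follow-up correlation is given. Results are therefore in units of the outcome SD, and r is assumed over a range.

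**The plan's own figure.** 20 × 1.25 = 25 per group, 50 in total, which reproduces. (25 × 0.75 = 18.75, slightly under 20. That is a separate matter; 20 per arm is used below.)

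**Planned comparison, n = 20 per arm.** Standard error = √(2/20) = 0.316 SD. The noncentral t with 38 degrees of freedom gives a difference detectable at 80% power of 0.91 SD.

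**Baseline-adjusted comparison.** Variance relative to the planned test = 1 − r². Estimating the slope multiplies this by (2n − 3)/(2n − 4) = 37/36 = 1.028, the penalty of about 3%. The detectable difference is close to 0.909 × √(adjusted ratio); the figures below use the noncentral t with 37 degrees of freedom.

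| Assumed r | 1 − r² | Cut in variance | Ratio with penalty | Detectable at 80% power |
|---|---|---|---|---|
| 0.3 | 0.91 | 9% | 0.935 | 0.88 SD |
| 0.5 | 0.75 | 25% | 0.771 | 0.80 SD |
| 0.7 | 0.51 | 49% | 0.524 | 0.66 SD |
| 0.8 | 0.36 | 64% | 0.370 | 0.55 SD |

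A simulation of 20,000 trials for each r gave variance ratios of 0.93, 0.76, 0.52 and 0.37, in line with the fourth column. At r = 0 the ratio was 1.03, so adjusting for a useless baseline costs about 3%.

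**Chance baseline difference, 20 per arm.** Its SD is also 0.316. The probability that it exceeds 0.5 SD in either direction is 2 × [1 − Φ(0.5/0.316)] = 0.114, about 11% of trials. A gap b shifts the unadjusted follow-up contrast by r × b on average. For b = 0.5 SD that is 0.15, 0.25, 0.35 or 0.40 SD at the four values of r.

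**Does the admission comparison catch this?** At 20 per arm it reaches p < 0.05 only when the observed gap exceeds 2.02 × 0.316 = 0.64 SD. If all 25 randomised per arm are compared, the threshold is 2.01 × 0.283 = 0.57 SD. A 0.5 SD gap passes as non-significant either way.

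**Type I error of the planned test.** In the same simulation the overall rate stayed between 4.6% and 5.2%. Among trials with a baseline gap above 0.5 SD it was about 8%, 13%, 21% or 28% for r = 0.3, 0.5, 0.7 or 0.8. Since the overall rate is about 5%, these trials are offset by better-balanced ones with a rate below 5%.

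**The case against.** **The planned test is valid.** Under randomisation the expected group difference in follow-up scores equals the expected difference in improvement, so the test does address the hypothesis. Its overall type I error is about 5%. This stands. A reader might infer from the conditional rates above that the trial is biased or that its false-positive rate is inflated. Neither follows: those rates describe the minority of trials with a large chance imbalance.

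**The size rests on an assumed correlation.** This also stands. A reader might infer that the trial throws away a quarter to two thirds of its information, or that most of the spread at follow-up is starting level. The first needs r of about 0.50 to 0.82 and the second needs r above 0.71; the article supports neither figure. The entry criteria (able to walk at least 6 metres, Mini Mental State Examination above 24) may narrow the baseline range, and the 3-month visit follows an unsupervised period. Both could lower r. At r = 0.2 the variance cut is only 4%.

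**Change scores may have been meant.** The Barthel outcome is described as an improvement, so this reading is not excluded. It is the less likely one: the sentence on within-group effects speaks of the same outcome data and mentions baseline explicitly, while the between-group sentence does not. Even then, covariance adjustment has variance (1 − r²)/[2(1 − r)] = (1 + r)/2 of the change-score analysis, or 0.65, 0.75, 0.85 or 0.90 at the four values of r. A change score improves on the unadjusted comparison only when r exceeds 0.5.

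**It is a pilot.** True, but it plans two-sided 0.05 tests, and the Discussion expects positive results to inform further guidance. Small groups are where chance imbalance and wide intervals matter most.

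**The normality rule.** A reader might think that it adds to the loss. That is not shown: a rank test without baseline leaves out the same information as the t-test.

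**Conclusion.** The point holds as one of efficiency and of exposure to chance imbalance. The article fixes a between-group test with no baseline term, although the baseline score on the same scale is collected before allocation and the question is improvement. That much rests on the text alone. The size is conditional on r: at 20 per arm the gain runs from slight (0.91 to 0.88 SD detectable at r = 0.3) to large (0.91 to 0.55 SD at r = 0.8). These figures assume roughly normal scores, equal variances and a linear relation with a common slope; bounded scales near their ceiling could depart from that. The change is worth making because the most it can cost in precision is about 3% of variance. It does not call the validity of the planned test into question.

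**What to change.** In the Statistical analysis section, make the primary between-group analysis of each continuous outcome, at 4 weeks and at 3 months, an analysis of covariance. The follow-up score is the response, group the factor, and the baseline score on the same scale the covariate. Report the adjusted mean difference with its 95% confidence interval. Keep the unadjusted t-test or rank test as a sensitivity analysis. If the residuals are clearly non-normal, use a method that keeps the baseline adjustment. Do not take a non-significant admission comparison as evidence of balance.

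The cost is one degree of freedom per model (about 3% of variance if r is 0), with no new visits, data or patients. The Ethics section requires a written application to the ethics committee for a protocol change. Trial status says that six participants have still to complete, and the data analysts are blinded to allocation, so the change can be fixed before unblinded analysis, but the application should go in soon.

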### Randomization and allocation concealment

This study is designed as a pilot study in which 20 participants will be included in each group. Allowing for a 25% dropout rate, we will recruit 25 patients in each group which means a total of 50 patients should be included during the whole trial[19, 20]. Participants will be assigned in a 1:1 ratio according to a computer-generated randomization list. Assignments will be sealed in opaque envelopes and will be opened by the study staff following informed consent procedures and baseline testing. The participants and researchers will know the allocated group, but the outcome assessors and data analysts will not.

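### The between-group test for each outcome is picked from the outcome data, so a primary scale can be analysed differently at 4 weeks and 3 months and its p-value can part from the reported means

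*Protocol article*

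**What the plan says.** All of the following is in the Protocol article.

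- **Default test (Statistical analysis).** Continuous outcomes are compared between arms by unpaired t-test and categorical ones by chi-square. The comparison is made twice: "data of all outcome measurements after 4 weeks and at the end of 3 months will be compared between the two groups".
- **Switch (same section).** "Nonparametric methods will be used when assumptions of normality are violated". The replacement method is not named.
- **Reporting (same section).** "the continuous variables will be presented as means and standard deviations", with no condition on which test is used. Also: "The statistical significance threshold will be set at 0.05 (two-sided), with 95% confidence intervals". The quantity that the interval describes is not named.
- **Scales (Primary outcomes).** All three primary scales are bounded. The lower-extremity Fugl-Meyer score has a maximum of 34 and the Berg Balance Scale runs from 0 to 56. For the Barthel Index: "The total score ranges from 0 to 100, with lower scores representing greater nursing dependency".
- **Size (Randomization and allocation concealment).** "This study is designed as a pilot study in which 20 participants will be included in each group", with 25 per group recruited to allow for dropout.
- **Patients (Inclusion criteria).** They must be able to walk at least 6 metres. No expected means or SDs are given for any scale.

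**The concern.** The switching sentence is a decision rule, not a detail left for later: the analysis of an outcome follows the observed distribution of that outcome. A separate analysis plan could name the normality check, but the choice would still come from the data unless that plan overrode the sentence.

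The two branches answer different questions. The t-test goes with a difference in means. A rank test asks whether scores in one arm tend to be higher, and its natural estimate is a shift. Two things follow.

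- One scale may be analysed by means at 4 weeks and by ranks at 3 months, so the two results are not the same kind of estimate.
- Where ranks are used, the reported means and SDs do not correspond to the p-value beside them.

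Bounded scales in recovering patients make skewed scores foreseeable. If scores approach the maximum, a better result in one arm itself makes the switch more likely. This is a pilot with no stated power calculation, offered as preliminary evidence of efficacy and feasibility. Its main efficacy product is therefore an effect estimate with an interval, which should be defined before the data are seen.

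**Working it through.** **The plan's own figure.** The only computed figure is the recruitment target: 20 × (1 + 0.25) = 25 per group, and 2 × 25 = 50. It is reproduced and not contested here. (A 25% loss from 25 leaves 25 × 0.75 = 18.75, so about 20 per arm is the right order for the checks.)

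**Inputs.** From the article: 20 per arm, two visits, scale maxima 34, 100 and 56, two-sided 0.05. Assumed, because the article gives none: SDs of 8 (Berg), 18 (Barthel) and 6 (Fugl-Meyer); effects of 0, 0.5 and 0.8 SD; correlation between visits 0.8; normal scores rounded and clipped at the scale limits. The normality check is also assumed: Shapiro-Wilk at 0.05 in each arm, with Mann-Whitney used if either arm fails. There were 2,000 simulated trials per setting (3,000 for the two-visit runs).

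**Step 1. Benchmark.** If scores are normal, two independent checks at 0.05 give a false switch in 1 − 0.95² = 0.0975, about 10% of trials.

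**Step 2. Chance of dropping the t-test at one visit.**

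| Control mean (Berg / Barthel / Fugl-Meyer) | No effect | 0.5 SD | 0.8 SD |
|---|---|---|---|
| Mid-scale: 34 / 55 / 18 | 0.10 / 0.13 / 0.10 | 0.10 / 0.13 / 0.10 | 0.09 / 0.13 / 0.10 |
| Moderately high: 42 / 70 / 24 | 0.10 / 0.18 / 0.12 | 0.21 / 0.33 / 0.29 | 0.45 / 0.58 / 0.55 |
| Near the ceiling: 46 / 80 / 27 | 0.30 / 0.54 / 0.40 | 0.71 / 0.88 / 0.79 | 0.91 / 0.99 / 0.95 |

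Two further simulations near the ceiling, with other assumed values and an effect of about 0.6 SD, gave 22-31% with no effect and 71-79% with it, and 25-43% and 78-92%. Higher still, the link with the effect fades because ranks are nearly always chosen: at Barthel 90 or Fugl-Meyer 30 with no effect the switch rate is already 0.98 or 0.93.

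**Step 3. Different tests at the two visits of one scale.** At 0.5 SD: Berg 42 then 46, 0.54; Barthel 70 then 80, 0.60; Fugl-Meyer 24 then 27, 0.57. Over all two-visit scenarios the range is 0.02 to 0.60.

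**Step 4. How far the two estimates differ** (mean difference against Hodges-Lehmann shift). They are close until scores are very near the maximum. Barthel 80 at 0.5 SD: 7.22 against 6.99. Berg 42 at 0.8 SD: 5.70 against 5.87. Beyond that, at 0.8 SD: Berg 50, 4.07 against 3.43; Barthel 90, 8.19 against 5.75; Berg 54, 2.81 against 1.25.

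**Step 5. Error rates on the primary scales.** Type I error is 0.044-0.059 for the switching rule and 0.043-0.059 for a t-test used throughout. Power at 0.8 SD is 0.55-0.71 and 0.53-0.71. The t-test and Mann-Whitney disagree on significance in 1-15% of runs.

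**Step 6. The fixed alternative.** On clipped scores a baseline-adjusted analysis held its size (0.039-0.053). At an assumed baseline correlation of 0.7 its standard error was 26-28% smaller; the unclipped formula gives 1 − √(1 − 0.7²) = 1 − 0.714 = 28.6%.

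**The case against.** The strongest reply is that this is a 50-patient pilot, the data analysts do not know the allocation, the statisticians are independent of the research team, and steps 4 and 5 show little inferential damage. That stands, and it limits the importance of the point.

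The reply is also right that the switch rates rest on assumed scores and on an assumed per-arm, per-visit check. The article does not say how or at what level normality is judged, and a condensed article may leave that to another document. If the decision were made once per scale for both visits, the first consequence would go. The choice would still come from the data, and a rank p-value would still sit beside means and SDs.

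A reader might go further than the text allows in four ways.

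- **That the confidence interval is most likely lost when Tai Chi works.** This needs scores near the ceiling. The walking criterion makes that plausible but does not establish it, and mid-scale the switch rate is unrelated to the effect.
- **That no interval would be available.** A rank-based shift interval can be given. A mean-difference interval can also be computed from the reported means, SDs and group sizes. The article never says that its intervals are for a mean difference; that is inferred from the t-test.
- **That the switch inflates type I error or costs power.** Step 5 shows neither.
- **That switching to ranks gives up the baseline score.** The planned unpaired t-test on visit scores does not use it either.

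**Conclusion.** The point holds with modest importance. The plan fixes a data-driven choice of test on three bounded primary scales at two visits, with means and SDs reported whichever branch is taken. The same scale can then be analysed differently at 4 weeks and 3 months, and a rank p-value does not correspond to the means shown with it.

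Under assumed means and SDs and a per-arm check, the switch occurs in about 10% of trials mid-scale whatever the effect. Near the ceiling it occurs in about 20-55% with no effect and 70-90% at 0.5-0.6 SD. Which range applies cannot be told from the article. The two estimates differ materially only very near the maximum. The cost is therefore to the consistency and interpretability of the preliminary effect estimate, not to error rates, and the switch gains almost nothing in return.

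**What to change.** For the three primary scales, replace the switching sentence with one analysis used at both visits whatever the distribution: the baseline-adjusted (ANCOVA) mean difference between arms with its 95% confidence interval. A heteroscedasticity-robust standard error or a permutation p-value can be specified if wanted. Add a rank-based analysis of each primary scale as a sensitivity analysis, reported whatever it shows. Treat the other continuous outcomes the same way unless a different fixed method is named for them in advance; the simulations tabulated above cover only the primary scales, so a different choice for the gait parameters or the stroke severity score may be reasonable.

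The cost is wording only, since baseline scores are already collected. The Trial status section says that 6 participants have still to complete, so the change should be dated and made before allocation is revealed to the analysts. The one downside is that for a strongly skewed scale a mean difference describes the typical patient less well. The rank-based sensitivity analysis covers that.

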### Informed consent

Prior to the study, the general study process and the responsibilities of both participants and researchers will be explained to potential participants. They will be told that their entry into the trial is entirely voluntary and that they can withdraw at any time. In the event of their withdrawal, the data collected cannot be erased and will be used in the final analyses. Written informed consent should be obtained from each participant before any interventions related to the study are started. ZL will be responsible for obtaining informed consent from all participants.

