### Adverse events

All unexpected adverse events during the intervention period will be reported, and the causality related to the Tai Chi intervention will be analyzed. If any adverse event occurs, the Tai Chi instructor or study managers will provide the corresponding treatment to the participant. The adverse events will be immediately reported to the primary investigator and ethics committee to decide if the participant needs to withdraw from the trial. In case of stroke recurrence or other worsening conditions, patients will be stopped from participating in the study and will be referred for further treatment.

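### Randomised patients with missing data before week 4 are dropped and intention-to-treat is conditional on 3-month loss, so no all-randomised analysis is stated for the 4-week comparison

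*Protocol article*

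**What the plan says.** Two consecutive sentences in the protocol article, Statistical analysis, set the rule: "Patients with missing data before 4 weeks will be eliminated", followed by "We will also conduct an intention-to-treat analysis if participants are lost to follow-up at 3 months". The same section plans between-group comparisons of every outcome at 4 weeks and at 3 months, by unpaired t-test or a nonparametric substitute.

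Four other statements bear on it:

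- Randomization and allocation concealment: the envelopes "will be opened by the study staff following informed consent procedures and baseline testing".
- Same section, on blinding: "The participants and researchers will know the allocated group, but the outcome assessors and data analysts will not".
- Informed consent: "In the event of their withdrawal, the data collected cannot be erased and will be used in the final analyses".
- Adverse events: "In case of stroke recurrence or other worsening conditions, patients will be stopped from participating in the study".

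On numbers, the randomization section says "This study is designed as a pilot study in which 20 participants will be included in each group" and "Allowing for a 25% dropout rate, we will recruit 25 patients in each group which means a total of 50 patients".

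**The concern.** The elimination rule selects patients on something that happens after randomisation. The only analysis named intention-to-treat is an addition, and its trigger is loss at 3 months, so loss before week 4 does not bring it into play. The comparison at the end of the supervised course therefore has no stated analysis of everyone randomised.

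Early loss could plausibly be both unequal and related to outcome. Patients know their group. The Tai Chi arm has a further session of 10 + 40 + 10 = 60 minutes after a conventional session of about 1 hour, five days a week for 4 weeks, which is 5 × 4 = 20 extra sessions. Patients whose condition worsens leave the study. If more of the patients who were doing poorly leave one arm than the other, a t-test on those who remain flatters the arm that lost more of them.

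The Discussion expects preliminary evidence on efficacy and feasibility, and says that positive results will contribute to guidance. Early loss is itself feasibility information, and the rule takes those patients out of the analysis.

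**Working it through.** **Step 1. Who is eliminated?** Envelopes are opened after consent and baseline testing. Anyone lost between then and week 4 has therefore been randomised and has baseline scores. Study design and setting schedules no assessment between baseline and 4 weeks, so such a patient normally has baseline scores only.

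**Step 2. Which analysis covers them?** At 4 weeks, none is stated. At 3 months, an intention-to-treat analysis is added if there is loss at that point. Its population is not defined.

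**Step 3. The consent statement beside the rule.** The consent statement concerns patients who withdraw and the data already collected from them. The elimination rule concerns patients with missing data before week 4. The two overlap for patients who withdraw before week 4: one text says their data will be used, the other says they are removed.

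**Step 4. The plan's own dropout figure.** 20 × (1 + 0.25) = 25 per group reproduces the stated 25 per group and 50 in total. Going from 25 recruited to 20 retained is a loss of 5/25 = 20%. A true 25% loss would leave 25 × 0.75 = 18.75 per group. The illustration uses 20%, because that is the loss that takes 25 to 20.

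**Step 5. Shift in one arm's mean.** Let a fraction q be removed, and let those patients have a mean m SD below the whole arm's mean μ. Then (1 − q) × retained mean + q × (μ − m) = μ, so

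shift = q × m / (1 − q).

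| q | m = 0.5 SD | m = 1.0 SD |
|---|---|---|
| 0.20 (5 of 25) | 0.2 × 0.5 / 0.8 = 0.125 | 0.2 × 1.0 / 0.8 = 0.25 |
| 0.10 | 0.1 × 0.5 / 0.9 = 0.056 | 0.1 × 1.0 / 0.9 = 0.111 |

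The values of m, the timing (all before week 4) and the restriction to one arm are assumptions. The documents give none of them. For scale, the standard error of the difference with 20 and 25 patients is √(1/20 + 1/25) = √0.09 = 0.30 SD.

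**Step 6. Upper bound and null cases.** If the patients lost are exactly those with the poorest outcomes, and outcomes are normal, the shift is φ(z_q)/(1 − q). With no true effect, the false difference is 0.35 SD for 5 lost against 0, 0.19 SD for 5 against 2, and 0 for 5 against 5.

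**Step 7. Simulation with no true effect** (25 per arm, t-test on those remaining, 5,000 runs per row; loss rates and odds ratios are assumed). The odds ratio is the increase in the odds of loss per SD of poorer outcome.

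| Loss, Tai Chi / control | Odds ratio | Bias (SD) | Type I error |
|---|---|---|---|
| 20% / 20% | 2 | 0.002 | 0.051 |
| 20% / 20% | 4 | 0.008 | 0.052 |
| 20% / 8% | 2 | 0.071 | 0.055 |
| 20% / 8% | 4 | 0.125 | 0.074 |
| 25% / 4% | 1 (unrelated) | −0.007 | 0.049 |
| 25% / 4% | 2 | 0.132 | 0.070 |
| 25% / 4% | 4 | 0.215 | 0.102 |

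The Monte Carlo error of a rate near 0.05 is √(0.05 × 0.95 / 5000) = 0.003. Bias needs both conditions: loss related to outcome, and loss that differs between arms.

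**The case against.** A reader might infer more than the documents support.

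- **That the consent statement and the elimination rule cannot both be followed.** The consent statement covers only withdrawn patients and only the data they have already given. Those are normally baseline scores, which could still enter the baseline comparison, and adverse events would still be reported. A t-test at 4 weeks cannot use a patient without a 4-week score. The texts are in tension and need reconciling, but they are not shown to be irreconcilable.
- **That the intention-to-treat set certainly excludes the early losses.** This is the natural reading of the two sentences together, but the population is undefined.
- **That the rule does bias the comparison.** Steps 6 and 7 show about zero bias with equal loss by the same mechanism, or with loss unrelated to outcome. The stopping rule applies to both arms, and nothing says it is the main route to missing data.
- **That a quarter of an arm will be lost before week 4.** The allowance applies to each group and is not tied to week 4. The 4-week course is given in hospital, and the unsupervised period comes afterwards.

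It can also be said that this is a declared pilot with no confirmatory claim, and that an analysis plan not shown here may add detail. The first lowers the severity. The second does not remove the point, because the article states a rule and does not merely leave one out.

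A mixed model is no full cure either. Baseline-only patients add little to the treatment estimate, and the model assumes missing at random, whereas exit caused by unrecorded worsening would not be.

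**Conclusion.** The point holds in limited form. The article fixes a completer comparison at 4 weeks and makes intention-to-treat additional and conditional on later loss. This can bias the arm comparison. On the assumptions of step 5, the shift is 0.13 to 0.25 SD for 5 of 25 lost and 0.06 to 0.11 SD for 10% lost, against a standard error of about 0.30 SD. It favours whichever arm loses more of its poorer patients. Under symmetric or outcome-independent loss it is about zero. The actual number, timing and reasons of early losses are not given. This should be fixed, but in a pilot with an unknown number of early losses it does not invalidate the trial.

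**What to change.** Replace both sentences with an unconditional rule along these lines: *the primary analysis at 4 weeks and at 3 months includes every randomised patient in the group assigned, whether or not the course was completed.* Then:

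1. Name the missing-data method. One suitable choice is a linear mixed model per scale with baseline, 4-week and 3-month scores in the response vector, stated to be valid under missing at random. Other all-randomised methods would also serve.
2. Add a sensitivity analysis that gives unfavourable values to patients who left for recurrence or worsening, since the mixed model does not address that mechanism.
3. Label any analysis without the early losses a completer analysis.
4. Report losses by arm, time and reason.
5. Reconcile Informed consent with Statistical analysis by saying how withdrawn patients' collected data enter the analyses.
6. If stopped patients are to be invited to outcome assessments, reconcile this with Adverse events, which ends their participation in the study. This concerns measurement only and leaves the clinical stopping rule as it is.

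The cost is some rewording and a little more analysis, settled before the analysts are unblinded. The estimate may be less favourable than the completer one. Trial status says that 6 participants have yet to complete, so item 6 could recover few outcomes. The analysis wording can still be changed.
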